# **STUDY POPULATION**

##

## **Participants**

Sixty COVID-19 confirmed cases (using the RT-PCR test) will be enrolled in the trial between April 9^th^ to April 14^th^ 2020. Sixty patients will be randomly assigned in a 1:1:1 ratio to one of the three following therapeutic regiments; 20 were assigned to the IFNβ1a group; 20 were appointed to the IFNβ1b group, and the remaining 20 were assigned

to the control group.

## **Inclusion Criteria**

- Age ≥ 18
- COVID-19 Confirmed Cases by Means of RT-PCR
- Oxygen saturation (SPO2) ≤ 93% OR respiratory rate ≥ 24
- At least one of the following: Calibrated contactless infrared forehead thermometry temperature of ≥37.8, cough, sputum production, nasal discharge, myalgia, headache or fatigue on admission.
- Time of onset of the symptoms should be acute (Days ≤ 14)

## **Exclusion Criteria**

- Refusal to participate expressed by patient or legally authorized representative if they are present
- Patients with prolonged QT or PR intervals, Second or Third Degree heart block, Arrhythmias including torsade de pointes
- Patients using drugs with potential interaction with Hydroxychloroquine + Lopinavir/Ritonavir, Interferon-β 1a، Interferon-β 1b.
- Pregnant or lactating women.
- History of alcohol or drug addiction in the past 5 years.
- Blood ALT/AST levels > 5 times the upper limit of normal on laboratory results.

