**Participants:**

Sixty COVID-19 confirmed cases (using the RT-PCR test) will be enrolled in the trial between April 9^th^ to April 14^th^ 2020. Patients will be randomly assigned to the intervention groups or the control group with the following eligibility criteria: ≥ 18 years of age AND (oxygen saturation (SPO2) ≤ 93% OR respiratory rate ≥ 24) AND at least one of the following: Contactless infrared forehead thermometer temperature of ≥37.8°C, cough, sore throat, nasal congestion/drip, myalgia, headache or fatigue on admission, and onset of the symptoms should be acute (Days ≤ 14). Although Hydroxychloroquine will be administered in a single dose, patients with heart problems (prolonged corrected QT (450 milliseconds) or PR intervals, second- or third-degree heart block, and history of arrhythmias including torsade de pointes) will be excluded. Other exclusion criteria include using drugs with potential interaction with Hydroxychloroquine + Lopinavir/Ritonavir, Interferon-β 1a, Interferon-β 1b, pregnant or lactating women, history of alcohol or drug addiction in the past 5 years, blood ALT/AST levels > 5 times the upper limit of normal on laboratory results and refusal to participate.

This study will be undertaken at the Loghman Hakim Hospital, Shahid Beheshti University of Medical Sciences.

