## **Study Drugs**

- **Hydroxychloroquine:**

400mg bid for first day then 200mg bid for 10 days

- **lopinavir/ritonavir (Kaletra):**

400mg/100mg bid for 10-14 days

For those that could not get orally:

5-ml suspension bid for 10-14 days

- **Interferon beta-1a:**

SC injection 44 micro-gram for 3 days (on days 1,3,6)

- **Interferon beta-1b:**

SC injection 0.25 mg for 3 days (on days 1,3,6)

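### The summary and the body state the eligibility rules differently (cardiac exclusion, the hydroxychloroquine course cited beside it, qualifying symptoms), so the same patient can be classified differently

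*Protocol*

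**What the plan says.** **Cardiac exclusion.** Under Participants, the Protocol Summary excludes "prolonged corrected QT (450 milliseconds) or PR intervals, second- or third-degree heart block, and history of arrhythmias including torsade de pointes". The figure carries no comparison sign and no correction formula is named. The formal Exclusion Criteria under Study Population read "Patients with prolonged QT or PR intervals, Second or Third Degree heart block, Arrhythmias including torsade de pointes".

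**Hydroxychloroquine.** The summary leads into its cardiac exclusions with "Although Hydroxychloroquine will be administered in a single dose, patients with heart problems". Study Design, General, likewise gives one 400 mg dose on day 1 in all three arms. Study Drugs gives "400mg bid for first day then 200mg bid for 10 days".

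**Qualifying symptoms.** The summary and the Inclusion Criteria each require at least one item from a list of symptoms or signs on admission. The summary's list contains sore throat but not sputum production. The Inclusion Criteria contain sputum production but not sore throat.

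**The concern.** The cardiac exclusion is a safety screen applied before randomization to all three arms. A summary normally shortens the body. Here the only QT figure is in the summary, and the formal list that staff would screen from has no operational QT rule. The arrhythmia item also changes in meaning, because the summary refers to history and the formal list does not.

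The summary mentions hydroxychloroquine exposure when it introduces this screen, and another section contradicts that exposure. The symptom lists then differ on who qualifies at all.

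At stake is whether a given patient was eligible or a protocol deviation. If that depends on which page was used, the enrolled population and the list of deviations cannot be stated without dispute. A statistical analysis plan would not ordinarily settle eligibility wording or a treatment course.

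**Working it through.** The Protocol gives no figure of its own to reproduce on this point. The check is a comparison of the texts, with two small calculations.

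**1. Cardiac items side by side**

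| Item | Summary, Participants | Exclusion Criteria | Same? |
|---|---|---|---|
| QT | corrected; 450 ms; no comparison sign or formula | prolonged; correction and threshold not stated | same condition, less specific in the formal list |
| PR | prolonged, no threshold | prolonged, no threshold | yes |
| Heart block | second or third degree | second or third degree | yes |
| Arrhythmia, including torsade de pointes | history of | no reference to history | can be read differently |

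On a literal reading, a past, resolved arrhythmia is excluded by the summary but not clearly by the formal list. A first arrhythmia found at admission is the reverse.

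**2. QT illustration.** The Protocol names no correction, so both formulas below are assumptions, and it reports no heart rates. The measured QT equivalent to a corrected QT of 450 ms is 450 × (60/HR)^k, with k = 1/2 (square root, Bazett) or k = 1/3 (cube root).

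| Heart rate (bpm) | Square root (ms) | Cube root (ms) |
|---|---|---|
| 50 | 493 | 478 |
| 60 | 450 | 450 |
| 80 | 390 | 409 |
| 100 | 349 | 380 |
| 120 | 318 | 357 |

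For example, at 100 bpm 450 × √0.6 = 349 and 450 × 0.6^(1/3) = 380. Two things follow:
- If staff compared a raw QT with 450 ms, their classification could differ from the summary's at any rate other than 60 bpm. The formal list does not state such a rule.
- Even within the summary's own rule, a measured QT between 349 and 380 ms at 100 bpm is above 450 ms corrected by one formula and below it by the other. At exactly 450 ms, the missing comparison sign leaves the patient unclassified.

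**3. Hydroxychloroquine totals**
- Summary and Study Design: one dose, 400 mg in total.
- Study Drugs, with the 10 days following day 1: 2 × 400 + 10 × 2 × 200 = 800 + 4,000 = 4,800 mg.
- Study Drugs, with day 1 counted in the 10 days: 800 + 9 × 2 × 200 = 800 + 3,600 = 4,400 mg.
- Ratio to the single dose: 4,400/400 = 11 to 4,800/400 = 12.

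These cannot both describe the same regimen.

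**4. Symptoms.** A patient whose only listed symptom is sore throat meets the summary's requirement and fails the Inclusion Criteria. A patient whose only listed symptom is sputum production is the reverse. Temperature, cough, nasal symptoms (worded slightly differently), myalgia, headache and fatigue are in both lists.

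**5. Scale.** One disputed patient in an arm of 20 is 1/20 = 5% of that arm.

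**The case against.** The strongest reply is that the two cardiac lists name the same four conditions, and that both can be followed at once by reading the formal list with the summary's definition of prolonged QT. That stands for QT. A reader might infer that the formal list applies an uncorrected QT, or that the Protocol both admits and excludes the same patients. The text supports neither. The formal list is silent on correction, sets no competing limit, and nowhere says that a patient whom the summary excludes may be enrolled. The QT conversions therefore illustrate what the ambiguity could do under an assumed reading and formula; they are not evidence of a contradiction.

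On arrhythmia, an unqualified term can include past episodes. That is fair, and it makes the item ambiguous rather than contradictory.

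It can also be said that the dosing conflict is a separate matter, and that the summary applies its cardiac exclusions despite the single dose, so a longer course would not remove their rationale. Both points are right, and the formal list ties its cardiac rule to no dose. The conflict between the sections remains, and because the summary mentions the dose in the same sentence as the screen, the two are best corrected together.

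Finally, the symptom conflict affects only a patient whose sole qualifying item is sore throat or sputum production, and a single-center trial has no variation between sites. Both limit how often the problem would arise. Neither makes the text consistent.

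**Conclusion.** The point holds as an inconsistency between summary and body, at three strengths:

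- **Cardiac screen:** a difference in precision. The formal list cannot be applied uniformly on QT by itself and is ambiguous on past arrhythmia. PR and heart block agree.
- **Hydroxychloroquine course:** a direct contradiction, 400 mg in total against 4,400 to 4,800 mg on the Protocol's own figures.
- **Qualifying symptoms:** a direct conflict over two items, which matters only where one of them is the sole qualifying symptom.

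The number of patients affected is unknown, because the Protocol gives no data on heart rate, QT or symptom frequency. No sample size, power, alpha or analysis result changes. The point merits correction because it bears on patient safety and eligibility and costs little to fix. Which QT limit, arrhythmia rule or hydroxychloroquine course applies is not a statistical question, and no view is taken on it here.

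**What to change.** 1. Write one cardiac exclusion statement and use it word for word in the Protocol Summary and the Exclusion Criteria. It should say whether QT is corrected, by which formula if so, the threshold with its comparison sign, and whether current arrhythmia, past arrhythmia or both exclude.
2. Reconcile the hydroxychloroquine course across the Protocol Summary, Study Design (General) and Study Drugs, and make the summary's lead-in to the cardiac exclusions agree with it.
3. Use one symptom list in the Protocol Summary and the Inclusion Criteria.

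The clinical investigators decide the content of each. The cost is a wording amendment. Depending on their choices, a few more or fewer patients may pass screening.

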## **Drop Out**

In the event of developing an allergic reaction to the drug or the patient's refusal to cooperate, the participant will be considered as a dropout. Any other reason resulting in discontinuation of the therapeutic regiments would also be considered as a dropout.

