# **STUDY DESIGN**

**General**

This is a single center, open label, randomized, controlled, parallel group, clinical trial that will be conducted at Loghman Hakim Medical Education Center in conjunction with Shahid Beheshti University of Medical Sciences.

Eligible patients with confirmed SARS-Cov-2 infections will be randomly assigned in a 1:1:1 ratio to one of the three following therapeutic regiments: 1) IFNβ1a (Recigen) (Subcutaneous injections of 44μg (12,000 IU) on days 1, 3, 6) + Hydroxychloroquine + Lopinavir/Ritonavir (Kaletra) [IFNβ1a group], 2) IFNβ1b (Ziferon) (Subcutaneous injections of 0.25mg (8,000,000 IU) on days 1, 3, 6) + Hydroxychloroquine + Lopinavir/Ritonavir (Kaletra) [IFNβ1b group], and 3) Hydroxychloroquine (Single dose of 400 mg on day 1, orally, in all three arms) + Lopinavir/Ritonavir (Kaletra) (400mg/100 mg twice a day for 10 days, orally, in all three arms) [control group]. All three groups will receive standards of care consisting of the necessary oxygen support, non-invasive, or invasive mechanical ventilation.

Patients will be randomly allocated to three therapeutic arms using permuted, block-randomization to balance the number of patients allocated to each group. The permuted block (three or six patients per block) randomization sequence will be generated, using Package ‘randomizeR’ in R software version 3.6.1. and placed in individual sealed and opaque envelopes by the statistician. The investigator will enroll the patients and only then open envelopes to assign patients to the different treatment groups. This method of allocation concealment will result in minimum selection and confounding biases.

The present research is open-label (no masking) of patients and health care professionals who are undertaking outcome assessment of the primary outcome - time to clinical improvement.

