## **Statistical Methods**

Statistical analysis will be performed by R version 3.6.1 software. The total sample size was calculated according to the Latouche and colleagues approach for estimating sample size in survival analysis with 80% power, alpha=0.05, Hazard Ratio (HR) of 3.0 (as the ratio of the hazard rates of time to clinical improvement (TTCI) corresponding to the intervention group compared to the control group) and assuming that 80% of patients would reach the primary outcome (10). The calculations will be carried out using Package ‘powerSurvEpi’ in R and accounted for a dropout

rate of 15%. Overall 60 patients, will be needed for the study, 20 for each arm.

Frequency rates and percentages will be used for categorical variables, and Interquartile Ranges (IQRs) and median will be used for continuous variables. Kruskal-Wallis test will be used for comparing the continuous variables. The Wilcoxon signed-rank test will compare the before and after intervention effects. Moreover, Chi-Square test will compare the frequency of categorical variables. We will use Kaplan–Meier to analyze the TTCI (compared with a log-rank test).

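### The Drop Out rule equates stopping study treatment with leaving the study, with no exception, and so conflicts with death as an outcome and puts the as-randomised comparison at risk

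*Protocol*

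**What the plan says.** The Drop Out section of the protocol has two sentences. The first names two reasons: "In the event of developing an allergic reaction to the drug or the patient's refusal to cooperate, the participant will be considered as a dropout". The second is a catch-all: "Any other reason resulting in discontinuation of the therapeutic regiments would also be considered as a dropout". Neither makes an exception for death or discharge, and neither says what happens to a dropout's data.

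Other sections bear on this:

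- **Study Outcomes.** The primary event is discharge or a two-step decline on the ordinal scale, whichever comes first. Death is category VII of that scale.
- **Secondary Outcomes.** Mortality runs from randomisation to day 21. Discharged patients are followed remotely.
- **Study Design, General.** Hydroxychloroquine and oral lopinavir/ritonavir are given in all three arms, the latter for 10 days (10 to 14 days under Study Drugs). The trial is open label for patients and for those assessing the primary outcome.
- **Statistical Methods.** The sample size is said to have "in R and accounted for a dropout" "rate of 15%. Overall 60 patients, will be needed for the study, 20 for each arm". This is the only statistical use of the term.

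**The concern.** Stopping a drug and leaving a study are different events. A patient who stops treatment can still be observed, and the outcome still belongs to the arm assigned. The Drop Out rule turns the first event into the second.

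Three consequences follow from the text:

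1. A death before the end of the lopinavir/ritonavir course necessarily stops the regimen, so on a literal reading that patient is a dropout. Two sections earlier the same death is an outcome. The protocol says it enrols severe patients with reduced chances of survival, so such deaths are foreseeable.
2. Interferon allergy is a route to dropout that the control arm does not have. In an open-label trial, refusal to cooperate may also depend on the arm.
3. Staff who apply the rule may stop collecting outcomes once a patient carries the label. No later analysis can recover those data, whatever population it names.

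At stake is whether the hazard ratio compares the groups that were randomised or groups selected after randomisation for reasons related to arm and prognosis.

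**Working it through.** **1. What the sample size assumes about dropouts**

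Inputs, all from Statistical Methods: "estimating sample size in survival analysis with 80% power, alpha=0.05, Hazard Ratio (HR) of 3.0", with the ratio "corresponding to the intervention group compared to the control group"; "assuming that 80% of patients would reach the primary outcome"; 15% dropout. Allocation is 1:1:1 (General), so each pairwise comparison has half its patients in each arm. Sidedness is not stated; two-sided is assumed.

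- Events for one pairwise comparison: (1.960 + 0.842)² / (0.25 × (ln 3)²) = 26.01, rounded up to 27.
- Patients in two arms: 27 / 0.80 = 33.75, rounded up to 34, which is 17 per arm.
- With the allowance: 34 / 0.85 = 40, which is 20 per arm and 60 in three arms.

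The plan's figure of 60 is reproduced. A one-sided test would give 16 per arm, so the two-sided reading is the one that fits. The step from 17 to 20 per arm is the dropout allowance, and it makes sense only if dropouts are expected to bring no primary event.

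Power at a hazard ratio of 3.0 is Φ(√(0.25 × events) × ln 3 − 1.960):

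| Patients contributing, of 40 | Expected events | Power |
|---|---|---|
| all 40 | 40 × 0.80 = 32 | 87% |
| 15% lost | 40 × 0.85 × 0.80 = 27.2 | 82% |

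The loss of numbers alone is therefore minor and already budgeted. What matters is who is lost.

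**2. What removal could do to the error rate**

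Assumptions, none of them from the protocol except the arm size and the 80%: no true effect; 20 against 20; exponential times with 80% improved by day 21 (rate −ln(0.2)/21 = 0.077 per day); log-rank test at two-sided 0.05; removed patients left out of the analysis. Three of 20 is the plan's 15%. Figures come from runs of 2,000 to 6,000 trials, so small differences are simulation error.

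| Removed from one interferon arm | Removed from control | Share favouring interferon |
|---|---|---|
| none | none | about 2.5 to 3% |
| 3 at random | none | 3.4% |
| 3 from the slower half | none | about 6% |
| 3 slowest | none | about 21% |
| 3 from the slower half | 2 from the slower half | 3.1% |
| 3 from the slower half | 3 from the slower half | 2.0% |
| 3 from the faster half | none | 1.3% (6.2% favour control) |

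Random removal does almost nothing. Removal of slow improvers from one arm favours that arm, balanced removal largely cancels, and removal of fast improvers reverses the direction.

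**3. Which events the rule catches**

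| Event | Under the Drop Out section | Elsewhere in the protocol |
|---|---|---|
| Death during the oral course | dropout, read literally | scale category VII; mortality to day 21 |
| Early discharge | dropout only if it ends the oral course, which is not stated | primary event |
| Allergic reaction | dropout, named | adverse effect, recorded daily |
| Other reaction | dropout only if treatment stops | adverse effect, recorded daily |

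**The case against.** The strongest reply is that the rule only attaches a label. Nothing says that dropouts are excluded, censored or replaced, and the Kaplan–Meier and log-rank plan leaves nobody out. The analysis population is commonly set in a statistical analysis plan, which is not at hand. This stands. A reader might infer that the protocol excludes these patients and so has already broken the randomised comparison; the text does not support that. The 15% allowance does not prove it either, since plans inflate for dropouts whether they exclude or censor them.

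Other stronger readings also fail:

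- **That early discharges are dropouts.** Lopinavir/ritonavir is oral, and the protocol does not say that discharge ends the course.
- **That exclusions are unequal by design.** The rule names only allergy to the drug, every arm receives drugs that can cause reactions, and refusal can occur in any arm. Interferon adds a source of dropout; it does not make the control rate zero.
- **That tolerability failures are hidden.** Safety Assessments requires all adverse effects to be recorded, and side effects are compared across arms as a secondary objective.
- **That a false-positive share of 21% should be expected.** It needs exclusion, none from control, and the three slowest patients removed.
- **That follow-up already covers everyone.** The remote follow-up described is for discharged patients, not for those who refuse or leave.

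It may also be said that the specific outcome definitions make exclusion of deaths an unlikely reading. That is fair, but the two sections still conflict as written.

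What the reply does not remove is the rule itself. It is a definition the protocol has fixed, not a detail left for later, and it governs conduct at the bedside before any analysis plan applies.

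**Conclusion.** The point holds in limited form and should be fixed. The Drop Out section merges treatment discontinuation with leaving the study, without exception. Read literally it contradicts the protocol's own treatment of death as an outcome to day 21, and it includes one route to dropout that only the interferon arms have. The sample size is consistent with dropouts supplying no outcome: 17 per arm without the allowance, 20 with it.

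The bias is conditional: it arises if dropouts are removed or no longer followed. Its size and direction depend on who they are. In the illustrations the share of null trials favouring interferon runs from 1.3% (fast improvers removed) to about 21% (worst case), against about 2.5 to 3% with nobody removed. These figures rest on the assumed exponential times and on the patterns of removal chosen; they show what the rule permits, not what will happen.

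**What to change.** Rewrite the Drop Out section so that:

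- stopping study treatment is recorded with its date and reason, but is not a dropout;
- all randomised patients are followed for all outcomes to day 21 and analysed in the arm assigned;
- death and discharge count as outcomes, as the Study Outcomes and Secondary Outcomes sections already define them;
- the term dropout is kept for withdrawal of consent to follow-up or loss of contact, with censoring at last contact.

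This leaves the rules on when treatment stops untouched. The 15% allowance can stay as cover for true loss to follow-up.

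The cost is one paragraph, plus follow-up to day 21 of patients who stop treatment; the remote contact planned for discharged patients could serve those who agree to it. The downside is a slightly diluted effect estimate if many stop treatment. The gain, if all 20 per arm contribute, is power of about 87% rather than 82% at a hazard ratio of 3.0.

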# **RESTRICTIONs**

Our study has several limitations. The trial will be open-label and without a placebo-control group, which opens the possibility for risks of bias. Our trial will be carried out in a limited resource setting, where we have no access to the follow-up RT-PCT testing and quantitative Real-Time RT-PCR; therefore, therefore we could not determine the time to a negative RT-PCR test and the viral loads to shed further light on the effect of the studied drugs on viral dynamics. Finally, we will only enroll the severe patients with lower probabilities of survival; hence our findings cannot be extrapolated to all COVID-19 patients.

